#### 3.2 BSYJF Background

The Chinese herbal formula, such as BSYJF, has a long history of application to disease treatment for musculoskeletal disorders with “bone-invigorating” and “muscle-strengthening” functions in China. BSYJF is composed of 7 herbs, *Herba Epimedii* (Yinyanghuo in Chinese), *Radix Polygoni Multiflori* (Heshouwu in Chinese), *Herba Cistanches* (Roucongrong in Chinese), *Radix Astragali* (Huangqi in Chinese), *Rhizoma Drynariae* (Gusuibu in Chinese), *Herba Dendrobii* (Shihu in Chinese) and *Flos Chrysanthemi* (Juhua in Chinese) with a crude weight ratio in 10:6:6:10:6:6:6.

Animal studies support the notion that BSYJF could delay bone loss of femoral

cortical and cancellous bone with aging, improve the structure of the bone matrix, the area and depth of resorption lacunae and bone strength, inhibit osteoclasts desorption, increase trabecular thickness as well as osteoblast number in ovariectomy (OVX) or glucocorticoid -induced osteoporosis model. BSYJF also exerts its beneficial effect on muscles of low extremity (Song and Shi et al., 1995; Song and Shi et al., 1996; Shen and Xu et al., 1997; Song and Shi, 1997; Song and Song et al., 1997; Song and Shen et al., 1998; Zhang and Shi et al., 1999; Zhang and Shi et al., 1999).

Among BSYJF in the treatment of osteoporosis, total efficacy rate ((Total symptom score at baseline - Total symptom score post treatment) / Total symptom score at baseline ×100%) is 67.31%, and BMD is maintained in our precious observation (Song and Song et al., 1997).

### 3.3 Rationale

Recently, the BSYJF has been prescribed in the treatment of osteoporosis in postmenopausal women. Moreover, those component herbs in BSYJF have been also prescribed by Chinese Medicine Practitioners in the treatment of musculoskeletal disorders through the centuries. However, the long-term effects of BSYJF on preventing falls and hip fractures associated risk factors have not been established. In this study, we will perform a double-blind and placebo-controlled trial to evaluate the long-term effect of BSYJF on reducing bone-dependent risk factor (bone mass) and bone-independent risk factors (muscle mass and functional mobility) to prevent falls and hip fractures risk factors in late postmenopausal women with osteopenia.

## 4. STUDY PURPOSE

To assess long-term effects of BSYJF on hip fractures risk factors in treating late postmenopausal women with osteopenia.

## 5. TRIAL PLAN

### 5.1 Study Design

The study duration is from January 2000 to December 2004. Subjects will be randomly assigned to receive BSYJF (n=70) or placebo (n=70) with a 1:1 allocation ratio. The study will be carried out at the two sites (Orthopaedics and Traumatology Institute with Shanghai Academy of Traditional Chinese Medicine, and Shuguang Hospital). A total of 140 participants will be selected from two sites to participate in the study.

## 5.2 Study Ethics

This study complies with the principles of the Declaration of Helsinki. This trial is approved by IRB of Orthopaedics and Traumatology Institute with Shanghai Academy of Traditional Chinese Medicine (Appendix A).

## 6. SUBJECT ELIGIBILITY

### 6.1 Inclusion Criteria

- (1) Women with at least 10 years after natural menopause, and aged from 55 to 69 years;
- (2) Osteopenia at least 12 months (T-score between  $-2.5$  and  $-2$  SD at femoral neck).

### 6.2 Exclusion Criteria

The postmenopausal women will be excluded from this study if:

- (1) Who had been diagnosed as having a neurological or musculoskeletal disorder, or coexisting chronic diseases;
- (2) Who have taken estrogen and calcitonin, fluoride, bisphosphonates, or adrenocortical hormone within one year;
- (3) Who had been took  $\geq 4$  prescription medications;
- (4) has environmental hazards for falls or tripping;
- (5) has impairment in gait;
- (6) has postural hypotension: drop in systolic blood pressure  $\geq 20$ mmHg or to  $< 90$ mmHg on standing;
- (7) has impairment in transfer skills or balance;
- (8) has impairment in leg or arm muscle strength or range of motion (hip, ankle, knee, shoulder, hand, or elbow) ;
- (9) has ALT or AST levels greater than 50% of upper normal limit; serum creatinine levels greater than  $133\mu\text{mol/l}$  or  $1.5\text{ mg/dl}$ .

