### 7.2 Methods of Enrollment

The recruitment goal is a total sample size of 140 participants. Researchers

at each site will identify qualified participants for the trial from clinical records based on the specified inclusion and exclusion criteria. Medical record reviews of existing databases can be done initially by setting up the searches using the matched eligible criteria. Potential participants will be also contacted by outreach materials or approached person at the clinic to determine their interest in the study. They will be briefly told about the study, and they will be invited for screening and informed consent if interested.

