### 10.2 Placebo Capsules

Placebo requires no active components, which will not be used for reproducing the real efficacy of BSYJF. Therefore, mimicking the original color and taste of the BSYJF without adding any active components is a difficult procedure. The main ingredients in placebo capsules are starch supplemented with food colorants and flavoring agents to mimic BSYJF capsules. Placebo capsules are asked identical to BSYJF capsules in size, appearance, color, favor and weight.

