### **17.2 Diet and Exercise Control**

During the entire trial, the subjects will be advised to follow the guideline for daily dietary intake and physical activities, such as intaking high-protein diet, avoiding alcohol abuse and smoking, and keeping active in daily physical activities. The questionnaire for daily dietary intake and physical activities (DDIPA; Appendix F) should be recorded at 12, 24, 36 months during 36-month clinical trial. Calcium and vitamin D supplement on their own should be prohibited in 36-month clinical trial.

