**Rationale:**

In the vast majority of cases, a hip fracture is a fragility fracture due to a fall or minor trauma in someone with osteoporotic bone. Risk factors of hip fractures observed are expected to be of long duration. However, BSYJF treatment was designed initially 36 months. Instead, a 10 year extension phase is added to explore the effect of transitioning from 36 months of treatment. The main objective of this extension phase is to evaluate if latent effects of BSYJF that might be lower fall rate and even hip fracture rate. In other words, 10 years extension follow-up of treatment cessation can be studied and is an accepted clinical approach.

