### Section: 6.2. Exclusion Criteria

Add:

**For the extension phase, additional exclusion criteria have been defined to protect subjects who have experienced a large bone loss or fragility fracture during the initial 36 month treatment phase of the study.**

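### The one-year entry washout omits BSYJF and its component herbs, so users of the test product may enter the placebo arm and attenuate the falls difference

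*Supplement*

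**What the plan says.** Section 6.2, exclusion (2), reads "Who have taken estrogen and calcitonin, fluoride, bisphosphonates, or adrenocortical hormone within one year". The Amendment 2 synopsis repeats it without change. The only exclusion that Amendment 2 adds concerns the extension phase: "additional exclusion criteria have been defined to protect subjects who have experienced a large bone loss or fragility fracture".

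Section 3.3 gives the background use: "Recently, the BSYJF has been prescribed in the treatment of osteoporosis in postmenopausal women", and "those component herbs in BSYJF have been also prescribed by Chinese Medicine Practitioners in the treatment of musculoskeletal disorders". Section 3.2 lists the seven herbs and cites the investigators' own earlier clinical observation of BSYJF.

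On recruitment, section 7.2 says that researchers at each site "will identify qualified participants for the trial from clinical records". It also allows outreach material and direct approach in the clinic. Section 5.1 names the two sites, and section 9.1 says that one of them, Shuguang Hospital, makes and distributes the capsules.

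During treatment, section 17.2 restricts only this: "Calcium and vitamin D supplement on their own should be prohibited in 36-month clinical trial". Medication history is taken at screening (section 7.4), and Table 1 records combined disease and medications at screening and at months 12, 24 and 36. No section excludes, washes out, stratifies by or adjusts for use of BSYJF or its herbs outside the trial.

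**The concern.** A placebo comparison needs a placebo arm free of the test product, or at least a record of how far it is not. As written, a woman who took BSYJF until the week before screening is eligible, while one who took a bisphosphonate ten months ago is not. If the first woman is allocated placebo, she may carry over some of the effect under test. If she goes on obtaining the product elsewhere, no rule is broken, and the compliance measure in section 14 would not show it, because it counts only leftover trial capsules.

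Randomisation spreads such women over both arms on average. The expected result is therefore an attenuated falls difference and lost power. The same would apply to the comparison of falls in the 10-year extension.

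**Working it through.** **Inputs.** Section 11 gives a placebo fall incidence of 19%, a 50% annual reduction (hence 9.5%), 55 per group before dropout, 20% dropout and 70 per group recruited. It sizes one-sided at 5% for 90% power. The analysis section tests two-sided at 5%. Amendment 1 deletes only the bone-density, muscle and mobility part of section 11, so the falls part stands. I read 19% as an annual risk and take the outcome as any fall, as the chi-square test suggests.

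**The plan's own figure.** The dropout step holds: 55/0.8 = 68.75, so 69, stated as 70. The 55 does not follow from the stated inputs. At 90% power, one-sided 5%, 19% v 9.5% needs 231 per group, and risks compounded to 36 months need 89. The nearest match is the annual risk simply tripled (57% v 28.5%) with continuity correction, which gives 57; the plan does not state this. The mismatch is a separate matter, but it means the baseline power must be computed afresh.

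**36-month risks.** With a constant yearly risk r, the 36-month risk is 1 − (1 − r)^3:
- placebo: 1 − 0.81^3 = 46.9%
- BSYJF: 1 − 0.905^3 = 25.9%
- difference: 21.0 points

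**Dilution.** Let f be the share of women who are users, and c the fraction of the BSYJF effect that users on placebo retain. Placebo risk becomes p1 − f·c·(p1 − p2). The BSYJF arm stays at p2, because every woman there receives BSYJF in the trial. The difference therefore shrinks by the factor (1 − f·c).

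**Power.** Power = Φ{[d − 1.96·√(2p̄(1 − p̄)/n)] / √([p1(1 − p1) + p2(1 − p2)]/n)}, with d the risk difference, p̄ the mean of the two risks and n = 55. With no users: pooled SE 0.0917, unpooled SE 0.0895, so Φ[(0.2098 − 0.1798)/0.0895] = Φ(0.335) = 63%.

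| f·c | Placebo risk | Difference (points) | Power, two-sided | Power, one-sided | N per arm, 90%, one-sided |
|---|---|---|---|---|---|
| 0 | 46.9% | 21.0 | 63% | 75% | 89 |
| 5% | 45.8% | 19.9 | 59% | 71% | 98 |
| 10% | 44.8% | 18.9 | 55% | 67% | 108 |
| 20% | 42.7% | 16.8 | 46% | 58% | 136 |

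Only the product f·c matters. The 5% row is 5% users with full carry-over or 10% with half; the 10% row is 10% with full or 20% with half.

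**Other readings of the risk.** Two-sided power at f·c = 0, 5%, 10% and 20%:
- annual risks (19% v 9.5%): 30%, 27%, 25%, 21%
- tripled risks (57% v 28.5%): 87%, 83%, 79%, 69%

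**The case against.** The strongest reply is that few such women may exist. Section 3.3 documents use for osteoporosis and musculoskeletal disorders, whereas the trial enrols osteopenia with a T-score of −2.5 to −2. It also excludes diagnosed musculoskeletal disorders, coexisting chronic disease and use of four or more prescription medications. This stands in part. These rules keep out some prior users, but exclusion (1) cannot cover osteopenia itself, which is an entry requirement, and exclusion (3) still admits a woman on three prescriptions. The T-score band also adjoins the condition for which BSYJF is prescribed.

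Second, full carry-over for 36 months fits continuing use better than past use, so for past use alone the higher rows are pessimistic. That stands. Third, if effects last for years, a one-year washout would not clear them. That also stands, and it is a reason to record exposure as well as restrict entry.

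A reader might infer more than the documents support:
- **That the recruiting clinics prescribe BSYJF.** Sections 3.2, 3.3, 7.2 and 9.1 make this plausible, but none says it.
- **That the plan assumes lasting effects and so contradicts itself.** Amendment 2 says "The main objective of this extension phase is to evaluate if latent effects of BSYJF that might be lower fall rate"; that is a question to be tested.
- **That prior use in the BSYJF arm also shrinks the difference.** The primary endpoint is falls at 36 months, not change from baseline, so this does not follow.
- **That prior use confounds the comparison.** It precedes randomisation, so it is balanced on average.
- **That past users would recognise the capsules.** Section 10.2 concedes that "mimicking the original color and taste of the BSYJF without adding any active components is a difficult procedure", but it then describes colouring and flavouring and asks for identical capsules. No section says that earlier prescriptions came as capsules.

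**Conclusion.** The gap is real and present in the latest version: neither the entry washout nor the on-trial restriction mentions the test product or its herbs, although the plan itself reports that they are in use. The consequence is possible attenuation of the falls difference, with no expected bias towards either arm.

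Its size cannot be fixed from the documents. At f·c = 5%, the loss is about 4 points of two-sided power on the 36-month compounded risks; at 20% it is about 17 points (63% to 46%). These figures assume a constant yearly risk, 55 evaluable women per arm, any fall as the outcome, and values of f and c that the plan does not give. The low starting power comes from the sample-size calculation, not from this gap, but it leaves little room for dilution. The case for change rests on how cheaply the gap closes, not on evidence that many users would enter.

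**What to change.** 1. In section 6.2(2) and the synopsis, add BSYJF and preparations of its component herbs (the section 3.2 list) to the existing list, under the plan's own one-year window. The medication history already taken at screening can be used to check this.
2. Record any use of BSYJF or its herbs outside the trial, with dates, in the combined disease and medications row of Table 1. Record use before the one-year window in the medication history.
3. Keep the intention-to-treat analysis of falls as primary, and prespecify a sensitivity analysis that accounts for such use. Leaving out women with recorded use before baseline keeps the randomised comparison. For use after randomisation, the planned time-to-first-fall Cox model could be censored at first use, with the caveat that such censoring may be informative.
4. Reconcile section 17.2, which restricts only self-taken calcium and vitamin D, with the aim of a placebo comparison free of the test product. What is or is not permitted during treatment is for the investigators to decide; the plan should state it.

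The cost is one amended criterion, a small addition to an existing form and a short analysis paragraph. Some clinic patients become ineligible, which slows recruitment slightly.

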## 7. SUBJECT ENROLLMENT PROCEDURES

### 7.1 Study Visit Definitions

Screening date is defined as the date that the ICF is signed. Enrollment date is defined as the date of randomization. The randomization must be completed within 2 weeks of the screening date (or re-screened within 2 weeks). If a subject's visit is delayed, her subsequent visit should not be shifted.

### 7.2 Methods of Enrollment

The recruitment goal is a total sample size of 140 participants. Researchers

at each site will identify qualified participants for the trial from clinical records based on the specified inclusion and exclusion criteria. Medical record reviews of existing databases can be done initially by setting up the searches using the matched eligible criteria. Potential participants will be also contacted by outreach materials or approached person at the clinic to determine their interest in the study. They will be briefly told about the study, and they will be invited for screening and informed consent if interested.

### 7.3 Informed Consent

Before subjects may be entered into the trial, the investigator requires a copy of the site's written IRB approval of the protocol. A single participant information sheet and consent form will be used for all the procedures done as part of the screening, baseline and follow-up (Appendix B).

The information sheet and consent form will be given to the potential participant and consent details will be explained, including trial's purpose, screening and study procedures, benefits and risks, confidentiality, rights, and trial contact information. The investigator obtaining consent will ask questions to the participant about her correct understanding the consent. The participant will be given the opportunity to review the document and any questions or concerns will be addressed. The participation is free of coercion or intimidation and no material compensation. All participants will be ascertained that they have the right to discontinue voluntarily from the study at any time, without penalty or loss of entitled benefits. If the participant agrees to take part in the trial, two copies of a signed consent form will be made, with the signatures of the participant and the site investigator. One copy of the consent form will be given to the individual to keep and another copy will be kept in a locked storage. For participants who are illiterate, the third party witness must sign ICF.

These consent procedures has been reviewed and approved by IRB. The Office of Scientific Research and Teaching will ensure proper collection and the ICF will be stored in a secure location.

### 7.4 Screening and Baseline Assessment

After ICF has been obtained at the first pre-randomization visit, the consented participant will undergo initial screening which will include basic medical and

medication history, and hip BMD measurement.

At the end of the first pre-randomization visit, the consented participant will be scheduled for a second visit within about 1 week for screening. The participant will be asked to do transvaginal ultrasound and blood test to check endometrial thickness, and kidney and liver function, etc. A venous blood sample (approx. 10 ml) will be taken for blood biochemistries and a urine sample to determine if the individual meets eligibility criteria. A screening log will be recorded by each site to each candidate.

The assessment will be included:

- Medical and medication history(including history of falls);
- Physical examination (including height and weight);
- 12-lead ECG;
- Vital signs: blood pressure, temperature, pulse and heart rate;
- DXA scan of proximal femur;
- Samples: blood count, liver and kidney function, 25 (OH) vitamin D, osteocalcin, 17 $\beta$ -estradiol and urine deoxypyridinoline;
- Safety.

At the third visit, those participants who meet the eligibility criteria will be enrolled in the trial and continue with a further baseline assessment and randomization.

All participants who enter into the screening period will receive a unique subject identification number. Participants numbers will be assigned in sequential order. The subject identification number must remain constant throughout the clinical trial, that's to say, it must not be changed at the time of re-screening, enrollment, or randomization. This number will not be the same as the randomization number assigned for the study. All the participants must be subjected to physical examination, efficacy and safety assessment during the recruitment.

## **8. RANDOMIZATION AND BLINDING**

### **8.1 Randomization**

All the participants will be randomly assigned to either BSYJF or placebo. Randomization numbers will be generated with random number tables by an independent statistician from the department of statistics, Shanghai University

of Traditional Chinese Medicine. This statistician is not involved in following data collection or analysis. The codes will be concealed in sealed, opaque envelopes with date and signature labels.

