## 8.2 Blinding

The blinding codes will be given to the pharmacist to keep and cannot be broken unless in emergency situations during the study. The treatment arrangements will be made by the pharmacist in each site, be blinded to the participants' characteristics and be not involved in the number generation and recruitment process.

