## 11. CALCULATION OF SAMPLE SIZE (This section has been amended. Please refer to the information in “Amendment” section.)

The estimated measurement variability in BMD, muscle (lean mass of left thigh) and functional mobility is 0.72, 0.89 and 0.89, respectively. The minimum expected difference in BMD between BSYJF and placebo is defined to be 0.5. Therefore, a minimum sample size of 37 for BMD, and 55 for lean mass of left thigh and functional mobility, respectively. Each group will provide 90% statistical power at the significance level of 5% in the one-sided test.

For falls, we hypothesize that BSYJF group will lead to an annual 50% reduction, and the incidence of falls among community-dwelling elderly women is considered to 19% in the placebo group according to the previous study (Aoyagi and Ross et al., 1998; Kannus, 1999). A sample size of 110 (55 per

group) is based on a one-sided significance level of 5%, and a power of 90%. Assuming the drop-out rate is 20%, 70 patients per group will be recruited for the trial.

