### **12.1 BMD and Muscle Measurement**

All the densitometry operators in the two sites should train specifically to ensure the following standard procedures. Left proximal femur (femoral neck and lean mass) in anteroposterior projection will be measured by DXA (DPX-L; Lunar, Madison, WI, USA). The same DXA apparatus should be used for a specific patient over the entire period. Monitoring of DXA scanner drift should be achieved by regular scanning of a calibration phantom.

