### Section: 5.1 Study Design

Replace:

The study duration is from January 2000 to December 2004. Subjects will be randomly assigned to receive BSYJF (n=70) or placebo (n=70) with a 1:1 allocation ratio. The study will carry out at the two sites (Institute of Orthopaedics and Traumatology, Shanghai Academy of TCM; and Shuguang Hospital). A total of 140 participants will be selected from two sites to participate in the study.

With:

**The study will be carried out from January 2000 to December 2014, comprised of a 36 month treatment phase and followed by a 10-year extension phase without treatment.** Subjects will be randomly assigned to receive BSYJF (n=70) or placebo (n=70) with a 1:1 allocation ratio. The study will carry out at the two sites (Institute of Orthopaedics and Traumatology, Shanghai Academy of TCM; and Shuguang Hospital). **At the beginning of the study, a total of 140 participants will be selected from two sites to participate in the study.**

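### Section 8.1 does not state the type of randomisation, any blocking or whether lists are kept per site, and site enters none of the stated analyses

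*Supplement*

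**What the plan says.** Sequence generation is covered in Section 8.1 alone: "Randomization numbers will be generated with random number tables by an independent statistician from the department of statistics". That statistician takes no part in data collection or analysis. On concealment, the section adds: "The codes will be concealed in sealed, opaque envelopes with date and signature labels". Section 8.2 says: "The treatment arrangements will be made by the pharmacist in each site"; the pharmacist is kept blind to participants' characteristics and has no part in generating the numbers or in recruitment.

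Neither amendment changes Section 8. No part of the document mentions simple randomisation, blocks, block size, stratification, a list per site or sequentially numbered envelopes.

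Section 5.1, as replaced by Amendment 2, sets the target: "Subjects will be randomly assigned to receive BSYJF (n=70) or placebo (n=70) with a 1:1 allocation ratio", with 140 women drawn from two sites. The number expected at each site is not given.

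The current analysis text (Section 16.3 as replaced by Amendment 1, and the synopsis in Amendment 2) names a chi-square test for falls and adverse events, Kaplan-Meier and Cox analyses of time to first fall, and repeated-measures ANOVA with *t*-tests on percentage change for the continuous outcomes. Site appears in none of them.

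**The concern.** The plan promises exact arm sizes and describes dispensing from two pharmacies, but does not say what kind of list would deliver either. Random number tables are a source of random digits. They can serve a coin-toss sequence, a list with fixed totals, or blocked lists for each site, and these schemes behave differently. A reader cannot tell which was meant, how one sequence would be shared between two pharmacies, or whether balance within sites is protected.

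The sites recruit their own participants and have their own densitometry operators. If the underlying risk of falling differs between the two populations, an unequal split of the arms within sites moves the raw comparison of falls, which is the only primary endpoint since Amendment 1. The planned chi-square test cannot adjust for that. What is at stake is some avoidable noise, and a randomisation method that cannot be described properly when the trial is reported.

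**Working it through.** **Inputs from the documents.** 140 women, 1:1, 70 and 70, two sites (Section 5.1 as replaced by Amendment 2); 55 evaluable per group and 20% dropout (Section 11).

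**Assumptions, because the documents give no figure.** 70 women per site; 36-month faller risks of 30% at one site and 50% at the other, the same in both arms.

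**1. The plan's own figure.** 55 / (1 − 0.20) = 68.75, rounded up to 69. The plan states 70 per group, which agrees to within one woman.

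**2. Overall split under simple allocation.** The number in one arm is Binomial(140, 0.5).
- P(exactly 70:70) = C(140, 70) / 2^140 = 0.067.
- P(63:77 or worse) = 0.27; P(60:80 or worse) = 0.108; P(58:82 or worse) = 0.052.
- If the tables were used to draw a list fixed at 70 and 70, P(70:70) = 1.

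**3. Precision lost through unequal arms.** Relative efficiency = 4·n1·n2 / 140². At 58:82 this is 4 × 58 × 82 / 19,600 = 0.971, a loss of about 3% of the information.

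**4. Balance within a site.** Under simple allocation the count in one arm is Binomial(site size, 0.5). Under one unstratified list fixed at 70:70 it is hypergeometric (140 in all, 70 in the arm, site size drawn). Chance that the arms differ by 10 or more:

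| Women at the site (assumed) | Simple allocation | One list fixed at 70:70 |
|---|---|---|
| 30 | 10% | 6% |
| 40 | 15% | 9% |
| 70 | 28% | 13% |
| 100 | 37% | 9% |

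**5. Effect on the falls comparison, 70:70 overall, 70 per site.** Let one arm have 35 + d women at the 30% site and 35 − d at the 50% site; the other arm has the reverse.
- Shift in the raw risk difference = 2d × (0.50 − 0.30) / 70 = 0.4d / 70.
- SD of d = √(70 × 0.25 × 70/139) = 2.97, so the 1 SD shift = 0.4 × 2.97 / 70 = 0.017, or 1.7 points.
- A 30:40 split (d = 5) gives 0.4 × 5 / 70 = 2.9 points.
- A 27:43 split (d = 8) gives 0.4 × 8 / 70 = 4.6 points, but a split at least that uneven has probability 1.1% under a fixed 70:70 list (7% under simple allocation).
- With site risks of 40% and 50% every shift halves: 1 SD is about 0.8 points, and the 27:43 split gives 2.3.

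**6. Comparison with sampling error.** At an overall risk of 40%, the standard error of the difference is √(2 × 0.4 × 0.6 / 70) = 0.083, or 8.3 points. Removing the between-site part leaves a mean within-site variance of (0.3 × 0.7 + 0.5 × 0.5) / 2 = 0.23 instead of 0.24, and a standard error of √(2 × 0.23 / 70) = 0.081. The gain is real but slight.

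**7. After the change.** With permuted blocks per site (size 4, for illustration only), the arms differ by at most 2 within a site and at most 4 overall. If both sites complete their blocks, the split is exactly 70:70.

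**The case against.** The strongest case against is that the plan is silent rather than wrong. A reader might infer that the randomisation is unblocked and unstratified, and that 70 per arm will therefore not be reached. The documents do not support this: Section 8.1 names only the source of the random digits, and stating 70 and 70 is consistent with a restricted list that always gives that split. A single list can also be divided into numbered ranges of envelopes for two pharmacies. The 7% holds only if allocation is simple. This objection stands in full.

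A reader might also infer that differences between the sites bias the treatment comparison. They do not. Chance imbalance is part of the random variation that an unadjusted test already allows for, and under the assumed risks the typical shift is about a fifth of the standard error. The documents give no site-specific fall risks, and falls are recorded at both sites under one definition and on one form. That stands too.

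A difference in level between the scanners is largely answered by the plan. Section 12.1 says "The same DXA apparatus should be used for a specific patient over the entire period", requires trained operators and phantom checks, and the BMD and lean-mass endpoints are changes from baseline, so a constant additive difference cancels.

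Finally, independent generation and concealment are both provided for, and leaving site out does not invalidate the test.

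None of this supplies what is missing. Even the favourable reading, one list fixed at 70:70, leaves a 13% chance of a difference of 10 or more in a site of 70, and no comparison makes use of site.

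**Conclusion.** The point holds as a gap in specification together with an easy improvement, not as an error that threatens the result. The plan does not say how the sequence is restricted, whether each site has its own list, or how 70 per arm is secured, and site is absent from all stated analyses.

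The size is modest. The 7% chance of an exact 70:70 split is conditional on simple allocation. The 28% and 13% chances of a within-site difference of 10 or more rest on an assumed 70 women per site. The typical shift of 1.7 points, against a standard error of 8.3, rests on assumed site risks of 30% and 50% and would be about half that at 40% and 50%. The loss of power from unequal arms is small: about 3% of the information at 58:82. The proposed method gives better balance and slightly better precision at almost no cost, and that is the reason to adopt it.

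**What to change.** **Section 8.1.** State the type of randomisation. Have the independent statistician prepare one list per site in permuted blocks of randomly varying size, held as sequentially numbered, sealed, opaque envelopes in each pharmacy. State the planned enrolment per site, so that the lists are consistent with 70 women per arm.

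**Section 16.3, and the synopsis to match.** Stratify the falls comparison by site, for example with a Cochran-Mantel-Haenszel test in place of the plain chi-square test. Stratify the Cox model by site. Add a site term to the models for BMD, lean mass and TUG.

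**Cost.** A different list and one stratification factor; no additional women, visits or measurements. If the list is already in use, leave it alone: record how it was produced and shared between the pharmacies, and add site to the analyses before unblinding.
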